## **10.Data handling conventions**

### Premature Withdrawal and Missing Data

If any subject withdraws prematurely from the study (prior to the final visit D90±7 days assessment), they are required to complete the withdrawal visit in the CRF. The reasons for withdrawal will be presented in a summary table. For the purposes of summaries and analysis of clinic visit data, this visit will be assigned to the next scheduled clinic visit for that subject, regardless of whether the date falls within the next visit window. Subjects who withdraw before the end of the study, but who do provide at least one

post-baseline measure for a particular endpoint, will be included in the analysis.

Subjects who do not attend any visits after randomization will be excluded from analysis of any endpoint, as no post-baseline data will be available.

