| 
Statistical considerations
 | 
All statistics will be 2-sided with <math>P < 0.05</math> considered significant.
 
 
1. Primary null hypothesis: in patients with TIA or minor ischemic stroke carried CYP2C19 LOF allele treated with aspirin 75 mg/d, there is no difference in 90-day risk of stroke (ischemic or hemorrhagic) in those treated with a 3-month regimen of ticagrelor initiated with a loading dose of 180 mg followed by 90 mg bid compared with a 3-month regimen of clopidogrel initiated with a loading dose of 300 mg followed by 75 mg/d when therapy is initiated within 24 hours of symptom onset.
 
2. Data set of statistical analysis: intention to treat (ITT)
 
3. Statistical analysis:
 
 
3.1 Balance of baseline characteristics (comparison between groups)
 
 
1) Continuous variables will be compared using t test or Wilcoxon rank sum test;
 
2) Categorical variables will be compared using a <math>\chi^2</math> test, Fisher exact test, or Wilcoxon rank sum test as appropriate.
 
 |

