#### **10.7 Possible event visit**

If a patient experiences a potential clinical neurological event, including a clinical deterioration that could be possibly related to ischemia, or new transient or persistent neurological symptoms, an adjudication packet will be produced by the site within 72 hours. This will include the following:

- A physical examination will be performed, including measurement of weight (kg) and vital signs (supine systolic and diastolic blood pressure, heart rate) and neurological examination;
- A neurological evaluation will be performed (Modified Rankin Scale and NIHSS);
- Brain CT or MRI (including T1 + T2 + DWI + FLAIR + ADC + GRE-T2\*); imaging data in DICOM format will be transferred to the core imaging evaluation lab. Brain CT is recommended for hemorrhagic stroke and MRI is recommended for ischemic stroke;
- If a patient experiences a new potential cardiac event, a cardiac evaluation (including ECG, myocardial enzymology and TnI) will be performed as clinically indicated. Information supporting a possible myocardial infarction will be collected in an adjudication packet and transmitted to Beijing Tiantan Hospital for further adjudication within 72 hours;
- Information will be collected on concomitant medications and adverse events since the last visit

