### **13.3.1 Analysis sets**

**Full analysis set (FAS):** FAS is the set for efficacy evaluation. All efficacy variables will be analyzed using the FAS. According to the ITT principle, the FAS includes

patients who are enrolled, randomized and have the record of at least one-day treatment of study drugs. Subjects with missing outcome data will be censored at the last follow-up assessment time (end of study or last visit preceding loss to follow up).

**Per Protocol set (PPS):** PPS includes subjects who completed study treatment without serious violation against protocol. Definition of serious violation against protocol will be confirmed at data review. Generally, it may include the following situations (but not limited to these situations): failure to meet the main inclusion criteria, concomitant treatment that seriously interferes with the evaluation of the efficacy of study drugs after randomization, poor compliance, and follow-up beyond the time window. PPS is the secondary analysis population for efficacy evaluation, ~~but~~ if its results are inconsistent with the full analysis set, detailed analysis of the inconsistent results is required.

**Safety analysis set (SS):** SS includes all patients who received at least 1 time of study drugs and safety assessment. Throughout the safety results sections, erroneously treated patients (eg, those are randomized to ticagrelor and aspirin group but are actually given clopidogrel and aspirin) will be accounted for in the actual treatment group.

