## **7. Analysis populations**

### **Full Analysis Set (FAS):**

According to the basic principle of intention-to-treat (ITT), all patients who were enrolled, randomized and had the record of at least one-day treatment of study drugs will be included. Subjects missing outcome data will be censored at the last follow-up assessment time (end of study or last visit preceding loss to follow up). This population will be the primary population for analyses of efficacy.

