## **12.Efficacy Analyses**

### **Primary Efficacy Analysis**

The primary endpoint is the rate of new stroke (both ischemic and hemorrhagic) reported during the 3 months treatment period. FAS will be the primary population for efficacy analyses. PPS will be used as secondary population for the efficacy analyses. If the results in the PPS population are inconsistent with the FAS population, detailed analysis of the inconsistent results is required.

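### The primary analysis is called intention-to-treat, but SAP v1.3 adds a dosing condition and a visit-attendance condition that permit a randomised patient with a known early stroke or death to be left out

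*Supplement*

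**What the plan says.** The synopsis of protocol v1.4 (Statistical considerations) gives intention to treat as the data set for analysis. Protocol section 13.3.1 then defines the FAS, under the ITT principle, as "patients who are enrolled, randomized and have the record of at least one-day treatment of study drugs". SAP v1.3 section 7 repeats the condition: "all patients who were enrolled, randomized and had the record of at least one-day treatment of study drugs will be included". The same paragraph deals with missing outcomes by censoring: "Subjects missing outcome data will be censored at the last follow-up assessment time". SAP section 12 makes this set primary: "FAS will be the primary population for efficacy analyses".

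SAP section 10 (Premature Withdrawal and Missing Data) adds a rule that is not in the FAS definition of either document: "Subjects who do not attend any visits after randomization will be excluded from analysis of any endpoint, as no post-baseline data will be available". Section 5 (Planned Analyses) says that membership of the analysis populations follows the rules in the SAP, so section 10 cannot simply be set aside.

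Events also reach the trial outside the day-21 and day-90 visits. For a suspected neurological event, protocol section 10.7 says that "an adjudication packet will be produced by the site within 72 hours". Section 11.5.2 requires serious adverse events, which include death, to be reported within 24 hours. Section 15.1 sends stroke and death to an independent adjudication committee. Section 7.6 keeps patients in follow-up after study drug is stopped.

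**The concern.** Both conditions are met or failed after randomisation, so the primary set is a modified ITT set whatever its label. The visit condition raises the larger question, for two reasons.

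First, it conflicts with the FAS text. One paragraph censors patients who lack outcome data; another excludes those with no visit. Two programmers could build different primary data sets from the same plan.

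Second, the stated reason for exclusion is that nothing was recorded after baseline. That need not be true of a patient who has a stroke or dies before discharge or day 21, because the event may be known from the packet or the safety report.

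The dosing condition raises a similar question. The safety set needs one administration of study drug, whereas the FAS needs one day of treatment. If one day is read as more than the loading dose, a patient with a stroke soon after that dose could enter the safety set but not the efficacy set.

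Treatment starts within 24 hours of onset in order to prevent recurrence, so the earliest events belong to the comparison. If exclusion depends on outcome, and outcome depends on arm, the comparison is no longer fully protected by randomisation. Blinding does not prevent this.

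**Working it through.** **1. The plan's own figure.** Inputs from SAP section 6: 9.4% v 7.1%, two-sided alpha 0.048, power 90%, 5% dropout. Allocation is 1:1 (protocol 7.2). With pooled variance and no continuity correction,

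n per arm = [z(0.976)·√(2·p̄·(1−p̄)) + z(0.90)·√(p0(1−p0) + p1(1−p1))]² / (p0−p1)², with p̄ = 0.0825,

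= [1.977·√0.15139 + 1.282·√0.15112]² / 0.023², which gives 3,038.

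3,038 / 0.95 = 3,198 per arm, or 6,396 in total. This matches the plan exactly. The exclusion rule does not alter the sample size.

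**2. When exclusion and censoring differ.** A log-rank or Cox analysis uses, at each event time, the patients still under observation. A patient censored at day 0 is in no risk set, so censoring and exclusion give the same result. The rule can therefore change the primary analysis only by deleting a known event or known event-free follow-up.

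**3. Size if known strokes are deleted.** The documents give no count, so the range is an assumption: 1 to 20 first strokes lost from an arm of 3,198 (0.03% to 0.63%). The test is a pooled two-proportion z, an approximation to the planned log-rank test:

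z = (p0 − p1) / √[p̄(1−p̄)(1/n1 + 1/n0)].

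Each deleted patient leaves both numerator and denominator. The threshold is two-sided 0.05, as SAP section 6 now sets it. The design case takes 9.4% and a 25% reduction (7.05%): 0.094 × 3,198 ≈ 301 strokes on clopidogrel and 0.0705 × 3,198 ≈ 225 on ticagrelor.

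| Starting strokes, ticagrelor v clopidogrel | Deleted | RR | z | p |
|---|---|---|---|---|
| 225 v 301 (design) | none | 0.748 | 3.46 | 0.0005 |
| | 5 / 10 / 20 from ticagrelor | 0.732 / 0.717 / 0.685 | 3.68 / 3.91 / 4.37 | all ≤ 0.0002 |
| | 5 / 10 / 20 from clopidogrel | 0.759 / 0.771 / 0.796 | 3.26 / 3.07 / 2.67 | 0.0011 / 0.0022 / 0.0076 |
| | 10 from each | 0.739 | 3.52 | 0.0004 |
| 257 v 301 (just not significant) | none | 0.854 | 1.95 | just above 0.05 |
| | 1 / 5 from ticagrelor | 0.851 / 0.839 | 1.99 / 2.16 | 0.046 / 0.031 |
| 256 v 301 (just significant) | none | 0.850 | 2.00 | just below 0.05 |
| | 1 / 5 from clopidogrel | 0.853 / 0.864 | 1.96 / 1.80 | 0.0504 / 0.072 |
| | 10 from each | 0.845 | 2.03 | 0.042 |

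Worked line: deleting one ticagrelor stroke from 257 v 301 gives 256/3,197 = 0.0801 against 301/3,198 = 0.0941, z = 1.99, p = 0.046.

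What matters is the difference between arms in lost events, not their total.

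**The case against.** A reader might infer that the plan removes known early fatal strokes from the primary analysis. The documents do not say so, and several passages point the other way:

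- The section 10 rule carries its own reason, the absence of post-baseline data. Where data exist, that reason is missing.
- The preceding sentence of section 10 keeps early withdrawals who have at least one measure after baseline for the endpoint. An adjudicated stroke could be read as such a measure.
- SAP section 10 (Time to Event Analysis) censors at death only when no event has occurred, so a fatal stroke is meant to count.
- Protocol section 10.7 calls the event contact a visit, section 10.8 gives it a column in the schedule, and section 10.3 describes a discharge visit that collects new strokes.
- Day 1 is itself a treatment day in protocol section 6.1, so a loading dose may satisfy the dosing condition.
- Assignment is double-blind, so never taking a first dose should not depend on arm.

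Most of this stands, and it limits the point to what the rules permit. It does not remove it. Protocol section 3.2 lists the face-to-face study visits as randomisation, day 21 and day 90. The event visit consists of examinations and scales that a patient who has died cannot attend, and a patient who dies in hospital may have no completed discharge visit. Nothing in the SAP says how these cases are classified. The blinding argument covers patients who never start drug, but not exclusions that follow from an early outcome.

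**Conclusion.** The point holds as a conflict between stated rules and as a permission to exclude. The primary set is labelled ITT but carries two conditions applied after randomisation. The visit condition contradicts the FAS censoring rule, and its rationale does not cover patients with a known early event. Whether any such patient would in fact be dropped depends on two readings that the documents leave open.

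The effect is confined to known events or known follow-up. At design rates it is probably small: across the assumed 1 to 20 strokes lost from one arm, p stays at or below 0.008, and equal losses barely move the estimate. It could matter at a borderline result if losses differ by arm, where a single stroke can move p across 0.05 in either direction. These figures rest on the assumed range and on a two-proportion approximation. A claim that the randomised comparison is broken would need evidence of differential loss, which the documents do not contain.

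Severity: moderate. The rule governs the primary population and gains nothing for a time-to-event analysis, so it should be settled before unblinding.

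**What to change.** Amend SAP sections 7 and 10, and protocol section 13.3.1 to match:

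- Define the primary efficacy set as all randomised patients, analysed as assigned, with time zero at randomisation.
- Count every adjudicated stroke from any source (scheduled visit, event packet or safety report), regardless of dosing or visit attendance.
- Censor event-free patients at last known contact, or at day 0 if there is none.
- Delete the no-visit exclusion for time-to-event endpoints.
- Keep the present FAS as a named sensitivity analysis, and state there whether a day-1 dose counts as one day of treatment.
- Report by arm the number of randomised patients who fall outside the present FAS or the visit rule, and the number of adjudicated events among them.

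The cost is wording and a small programming change. No new data are needed and the sample size is unaffected.

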## Event Rates

The number of people and person-time of events should be recorded in detail and showing the event rate in 90 days of each treatment group in summary statement.

The event rate for each treatment group will be calculated as: the sum of number of event for all the patients / the sum of number of treatment periods for all the patients.

## Time to Event Analysis

Differences between treatments in the risk of new stroke (ischemic or hemorrhagic) event and clinical vascular events during maximum 90-day follow-up were assessed using standard Kaplan-Meier time-to-event approaches. The time to the first event was used in the model when there were multiple events of the same type. Patients were considered censored at the time of study termination or death if there were no events occurred during the study.

# 11.Study Population

## Disposition of Subjects

The number of subjects in each analysis population will be presented, subjects to be excluded from the Per Protocol population will be listed, and the total number of subjects attending each clinic visit will also be summarized by treatment group.

The number of subjects randomized, completed and prematurely withdrawn from the study will be presented for each treatment group. The primary reasons for

withdrawal both prior to and post randomization will also be presented.

A data display listing and summary of deviations from the inclusion/exclusion criteria will be presented for all subjects who were either entered or randomized into the trial.

### Protocol Deviations

Subject data will be examined for evidence of protocol violators in order to assess how well the protocol was followed. Inclusion and exclusion criteria are detailed in the study protocol.

Subjects who commit protocol violations will be included in the FAS Population but excluded from the Per Protocol Population. These protocol violations will be shown in a listing. Subjects can either be full or partial protocol violators. A full protocol violator is completely excluded from the Per Protocol Population. A partial protocol violator has only some data excluded. For subjects who violated the protocol during the treatment period due to unpermitted changes in the medication or prohibited concurrent medication, the analysis will only use data recorded prior to the violation. For all violations which reference the treatment period, the treatment start date will be used as the reference date.

A listing of all possible protocol violators will be produced for clinical review. The final list of subjects who are protocol violators and are therefore excluded from the Per-Protocol population will be agreed by the study team.

### Demographic and Baseline Characteristics

The following demographic information will be listed and summarized for subjects in each treatment group: age, sex, body mass index (BMI). This will also be done for

Version 1.3

April 20 2021

stroke and TIA history, medical history, smoking history, alcohol use, symptoms of the index event, pretreatment Rankin Score and NIHSS score.

Vital signs including supine systolic blood pressure, diastolic blood pressure, and heart rate will also be listed and summarized in each treatment group.

The continuous data followed normal distribution will be presented as mean and standard deviation, and the continuous data followed skewness distribution will be presented as median and interquartile range; categorical data will be presented as n(%). T-test or Wilcoxon rank sum test will be used for comparison between two continuous data, and Chi-squared tests or Fisher exact test will be used for comparison between two categorical data.

## **12.Efficacy Analyses**

### **Primary Efficacy Analysis**

The primary endpoint is the rate of new stroke (both ischemic and hemorrhagic) reported during the 3 months treatment period. FAS will be the primary population for efficacy analyses. PPS will be used as secondary population for the efficacy analyses. If the results in the PPS population are inconsistent with the FAS population, detailed analysis of the inconsistent results is required.

### **Main Model**

The time to first new stroke (ischemic stroke or hemorrhagic stroke) reported during the 3 months treatment period for the FAS Population will be summarized by treatment group using Kaplan-Meier estimates. The hazard ratio for the treatment comparison will be derived using a Cox proportional hazards model, including the pooled study center as a random effect. The hazards ratios with 95% CI will be reported. This will also be presented graphically on a Kaplan-Meier curve. The log-rank test will be used

to evaluate the statistical significance of the treatment effect.

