## 6. Sample size estimates

The study hypothesized that there is no difference in 90-day risk of stroke (ischemic or hemorrhagic) in those treated with a 3-month regimen of ticagrelor initiated with a loading dose of 180 mg followed by 90 mg bid compared with a 3-month regimen of clopidogrel initiated with a loading dose of 300 mg followed by 75 mg/d when therapy is initiated within 24 hours of symptom onset in patients with TIA or minor ischemic

stroke carried *CYP2C19* LOF allele treated with aspirin 75 mg/d.

The minimum necessary sample size in the trial is established by the requirement to detect the smallest expected, clinically meaningful treatment difference comparing the treatment with placebo. Based on the genetic sub-analysis of the CHANCE study, we presume that the 90-day risk of stroke recurrence in *CYP2C19* loss-of-function allele carriers is about 9.4%, and 6.7% for noncarriers. With the point-of-care identification of the *CYP2C19* loss-of-function allele carriers to assess a proper pharmacogenetic approach for patients with high-risk TIA or MIS, we assumed a 25% relative risk reduction with alteration from clopidogrel to ticagrelor (90-day risk of stroke recurrence: 7.1%). Considering the potential impact of the interim analyses on the probability of type I error, we adjusted the statistical significance to a 2-sided  $\alpha$  of 0.048. With a sample size of 6,396 patients, we will have 90% power to detect a relative risk reduction (Ticagrelor: loading dose: 180mg, 90mg bid on day 2-90 vs. Clopidogrel: loading dose: 300mg, 75mg qd on day 2-90) of 25% and 5% dropouts (medication nonadherence). Assuming 58.8% prevalence of *CYP2C19* loss-of-function allele carriers in a Chinese population, we projected screening 10,878 patients would be necessary. Based on the results of interim analysis, the DSMB will recommend whether the sample size need to be re-calculated.

According to the DSMB meeting on April 7, 2021, the DSMB lookup the overall event rates of the trial and suggested not to unblind the treatment assignment in the interim analysis. Therefore, comparison of efficacy and safety outcome between two treatment groups were not performed in the interim analysis, and sample size was not re-calculated. The type I error level of the statistical significance will be set to a 2-sided  $\alpha$  of 0.05 in the final analysis.

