### **Interactions with Subgroups**

Summary tables will be produced for the predefined subgroups and interactions between treatment and these subgroups will be investigated, using a Cox proportional hazards model. A separate model will be used for each interaction to determine its significance. This will also be presented graphically on a forest plot.

The predefined subgroups including:

- Age (<65 years vs. ≥65 years)
- Gender (men vs. women)
- BMI
- Index event (TIA vs. minor ischemic stroke)
- Time from index event to randomization
- Etiological stroke subtype based on the TOAST Classification
- Diabetes mellitus
- Hypertension
- Type of *CYP2Y19* LOF alleles (intermediate metabolizers vs. poor metabolizers)
- Previous ischemic stroke or TIA
- Prior antiplatelet therapy
- Prior statin therapy
- Prior smoking status
- Location of symptomatic artery stenosis (Intracranial artery stenosis vs. extracranial artery stenosis)

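### The primary analysis uses no patient-level covariate: it is valid and meets its 90% power target, but forgoes a small, cheap gain in power

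*Supplement*

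**What the plan says.** SAP v1.3, section 12 (Main Model) summarises time to first new stroke by Kaplan-Meier. It derives the hazard ratio from a Cox model "including the pooled study center as a random effect" and tests the treatment effect with a log-rank test. No patient-level covariate and no strata are named for either. Protocol v1.4 (synopsis and 13.3.2) specifies Kaplan-Meier, Cox and log-rank, also without covariates. Neither document names a covariate-adjusted supportive analysis.

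The baseline data are available. SAP section 11 summarises age, sex, BMI, medical history, "pretreatment Rankin Score and NIHSS score". The subgroup list in section 12 includes age, index event type, time from event to randomization, diabetes, hypertension and "Previous ischemic stroke or TIA". Each is used only in its own interaction model.

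Protocol 7.2 describes 1:1 allocation from a central list and mentions no stratification factor.

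**The concern.** When outcome depends on known baseline factors, including them in a time-to-event model usually makes the treatment test somewhat more powerful and removes the effect of chance imbalance in those factors. Here the candidates are recorded anyway and no stratified randomization is described. The SAP plans between-arm tests of baseline characteristics but does not say what follows if a factor differs, so any adjusted analysis would be post hoc. At stake are a little power and a prespecified answer to a question that readers often ask. Type I error is not at stake.

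**Working it through.** **Inputs.** All design figures come from SAP section 6.
- Control risk: "loss-of-function allele carriers is about 9.4%, and 6.7% for noncarriers".
- Ticagrelor risk, 25% relative reduction: "with alteration from clopidogrel to ticagrelor (90-day risk of stroke recurrence: 7.1"%.
- Design alpha: "we adjusted the statistical significance to a 2-sided" 0.048.
- Final alpha: "The type I error level of the statistical significance will be set to a 2-sided" 0.05.
- Size: "With a sample size of 6,396 patients, we will have 90% power to detect a relative risk reduction" of 25%, with 5% dropout.

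**Step 1: reproduce the sample size.** Two proportions, pooled variance, no continuity correction:

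n per arm = [z(α/2)·√(2p̄q̄) + z(β)·√(p₁q₁ + p₂q₂)]² / (p₁ − p₂)²

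With p₁ = 0.094, p₂ = 0.071, p̄ = 0.0825, z(α/2) = 1.977 and z(β) = 1.282, this gives 3,038 per arm, or 6,076 in total. Then 6,076 / 0.95 = 6,396, an exact match. Power on 6,076 evaluable patients is 90.0% at alpha 0.048 and 90.3% at alpha 0.05. The target is met by a formula without covariates.

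**Step 2: which factors are known at baseline?** Age and index event type are eligibility items. Onset time is needed for the 24-hour criterion (protocol 5.1). Diabetes, hypertension and previous stroke or TIA belong to the history taken on Day 1 (10.2.1). TOAST subtype is recorded at discharge (10.3), and vascular assessment is due within 7 days of enrollment (10.8, note 5), so subtype and stenosis are not true baseline covariates. NIHSS is marked for minor-stroke patients only in the current schedule.

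**Step 3: what would adjustment add?** The documents give no prognostic strength, so a range is assumed: a normally distributed risk score with standard deviation s on the log hazard, C ≈ Φ(s/√2). For each s, 4,000 trials of 6,076 patients were simulated with marginal 90-day risks held at 9.4% and 7.1%. A Cox model with treatment alone was compared with one that also contained the score. Power = Φ(|mean Z| − 1.960). The marginal hazard ratio is ln(0.929)/ln(0.906) = 0.746.

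| s | C | mean abs. Z, unadjusted → adjusted | Power | Gain (points) | Equivalent saving in N | Conditional HR |
|---|---|---|---|---|---|---|
| 0.35 | 0.60 | 3.252 → 3.267 | 90.2% → 90.5% | 0.3 | 0.9% | 0.745 |
| 0.50 | 0.64 | 3.252 → 3.288 | 90.2% → 90.8% | 0.6 | 2.2% | 0.743 |
| 0.75 | 0.70 | 3.237 → 3.332 | 89.9% → 91.5% | 1.6 | 5.6% | 0.739 |
| 1.00 | 0.76 | 3.239 → 3.434 | 90.0% → 93.0% | 3.0 | 11.1% | 0.7325 |

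The saving in N is 1 − (unadjusted Z / adjusted Z)². A separate simulation (1,500 trials per setting, complementary log-log model) gave 1.6%, 3.6% and 5.7% more information for s = 0.4, 0.6 and 0.8. From 90% power, that is 90.4%, 91.0% and 91.5%.

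**Step 4: how large is chance imbalance?** With 3,198 per arm, the between-arm difference in a factor present in half the patients has SD √(2 × 0.25 / 3,198) = 0.0125. For an assumed factor hazard ratio of 1.5, this shifts the log hazard ratio by 0.0125 × ln 1.5 ≈ 0.005. With about 6,076 × 0.0825 ≈ 501 events, its standard error is about 2/√501 ≈ 0.089. A typical imbalance is therefore about 6% of one standard error.

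**The case against.** The strongest case for leaving the plan alone is that nothing in it is wrong. An unadjusted comparison in a 1:1 randomized trial is valid. It also matches the sample-size formula, the Kaplan-Meier display and the log-rank test. No passage promises adjustment, and no known stratification factor is left out of the model. All of this stands.

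Two further objections stand and shape the fix. First, the log-rank test decides significance, so adding covariates to the Cox model alone would leave the power of the deciding test unchanged. Second, that test is also written into the protocol, so moving the primary P value takes more than SAP wording.

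The size of the gain can also be questioned. It rests on assumed strength, uses one ideal score rather than several mostly binary covariates, and was measured against a model without the centre term that the plan has. Eligibility narrows the spread of risk, so the low end, about 0.3 points, is quite plausible. The reset of alpha from 0.048 to 0.05 returned about the same amount.

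The estimand objection carries less weight. The planned hazard ratio is already conditional on a centre effect, and the conditional and marginal values are within 0.007 of each other up to C = 0.70. Only at C = 0.76 does the gap reach about 0.013.

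**Conclusion.** The point holds as an optional improvement in efficiency. The primary analysis uses no patient-level covariate although six suitable ones are known by Day 1. It gives up about 0.3 to 1.6 points of power for an assumed C-statistic of 0.60 to 0.70, or about 3 points for a strong score (C = 0.76).

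A reader might infer more, and the documents do not support it:
- **That the trial is underpowered or biased.** It reaches its stated 90% without adjustment, and type I error is unaffected.
- **That every prognostic factor is available at baseline.** Etiologic subtype and stenosis are settled after randomization.
- **That unstratified randomization leaves a material imbalance problem.** At about 3,200 per arm the expected effect is negligible. What prespecification adds here is less discretion, not removal of bias.
- **That the gain is entirely free.** There are costs, though small ones.

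**What to change.** Before unblinding, amend the SAP section 12 Main Model as follows:
- Add fixed covariates to the Cox model and keep the pooled-centre random effect: age, TIA versus minor stroke, diabetes, hypertension, previous ischemic stroke or TIA, and onset-to-randomization time. Leave out TOAST subtype and stenosis.
- State the form of each covariate (for example, age and time linear, the others binary) and a simple rule for missing values that does not use treatment assignment.
- Take the primary hazard ratio, confidence interval and P value from this model. Keep the unadjusted log-rank test and Kaplan-Meier curves as supportive.
- Make the same change in protocol 13.3.2 and the synopsis, so that the two documents name the same deciding test.

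The timing allowed this. SAP v1.3 is dated April 2021 and records that treatment assignment was not unblinded at the interim, and three-month follow-up was planned to run to September 2021.

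The cost is a SAP and protocol edit, the missing-value rule, and a hazard ratio read as conditional on the covariates. If the sponsor prefers to keep the log-rank test as primary, the same model can be named as a supportive analysis. That fixes the covariate list in advance but adds no power to the deciding test.
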